###### Tertiary hypotheses: Compared with SA, the PA program

- Reduces the risk of the combined outcome of all-cause mild cognitive impairment or dementia (MCI/D);
- Improves performance on a composite measure of cognitive function;
- Improves physical performance within subgroups defined on the basis of ethnicity/race, gender and baseline performance;
- Results in improvements in measures of physical performance and walking speed that vary with the amount of intervention received;
- Improves sleep-wake disturbances and leads to a lower incidence of sleep-wake disturbances;
- Reduces dyspnea and improves ventilatory capacity;
- Reduces the risk of hospital admissions for exacerbation of airway disease (asthma, bronchitis, emphysema, &/or COPD) or pneumonia; and

- Reduces the risk of combined cardiovascular (CVD) events including:
  - Myocardial infarction (MI),
  - Angina requiring hospitalization,
  - Any stroke (ischemic or hemorrhagic),
  - Transitory ischemic attack (TIA) requiring hospitalization,
  - Hospitalization for carotid artery disease,
  - Hospitalization for congestive heart failure (CHF),
  - Hospitalization for peripheral artery disease (PAD) or outpatient revascularization for PAD,
  - Ruptured abdominal aortic aneurism (AAA), and
  - CVD death.

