#### **6.2.17. Pulmonary Questionnaires**

A modified version of the ATS-DLD-78-A questionnaire assesses respiratory symptoms, prior cardiopulmonary illnesses, occupational history, and smoking exposure (total of 11 questions, each having subsections) [ATS-DLD-78-A Adult Dyspnea Questionnaire. at <http://www.cdc.gov/niosh/respire.html>]. To reduce participant burden and overlap with other LIFE instruments, the modified version omits demographic information, cardiovascular history and family history of pulmonary illnesses. This modified instrument will require about 20 minutes to administer. At follow-up, the ATS-DLD-78-A will be further modified to include only respiratory symptoms, and smoking status (10 minutes).

In addition, the Borg index for Dyspnea, which assesses dyspnea, will be administered immediately after the 400 m walk each of the follow-up clinic visits.

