| EPrime cognitive assessment &                     |       |                | x              |                 |     | x & |                | x & |     |                |                 |     |
| Quality of well being (CEA)                                      |       |                | x              | x               | x   | x                  | x              | x                  | x   | X              |                 | x   |
| Health care utilization (CEA)                                    |       |                | x              | x               | x   | x                  | x              | x                  | x   | X              |                 | x   |
| Study Eligibility Checklist                                      |       |                | x              |                 |     |                    |                |                    |     |                |                 |     |
| NEWS-A                                                           |       |                | x              |                 |     |                    |                |                    |     |                |                 |     |
| Ankle Brachial Index (ABI)                                       |       |                | x              |                 |     |                    |                | x                  |     |                | x ** |     |
| Claudication questionnaire                                       |       |                | x              |                 |     |                    |                | x                  |     |                | x ** |     |
| Sleep-wake disturbances                                          |       |                | x              | x               |     | x                  |                | x                  |     |                |                 |     |
| Pulmonary questionnaires, ventilatory capacity                   |       |                | x              | x               |     | x                  |                | x                  |     |                |                 |     |
| Phlebotomy/Blood Processing/Urine                                |       |                | x @ | x @@ | x   |                    | x              |                    |     |                |                 |     |

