Scr=Screening visit; V=Visit; Rnd=Randomization; F=follow-up visit; Cls=Close out visit; CEA=Cost Effectiveness Analysis; PIV=Post intervention visit; ~The SPPB test is administered when the 400 m walk test is not attempted. \*CHAMPS-18 can be completed during group information/screening sessions prior to SV1; \*The Cancer Follow-up Form and Cardiovascular Medical History Baseline Form can be collected during a subsequent follow-up visit during the first 24 months if not collected prior to randomization.a An abbreviated Disability Questionnaire will be administered at the 18, 30, and 42 month visits. \*The 400 m walk test can be administered either at the end of SV1 or at SV2; ^Only 1 of the measures needs to be completed immediately after the 400 m walk: Efficacy for Walking; the others should be completed at SV2; #Accelerometry is performed in all participants at each site in conjunction with the 400 m walk; °Participants who do not complete the cognitive battery at the 24 month visit or PIV will be administered the Telephone Interview of Cognitive Status (TICS). For those participants that do not complete the TICS or who score < 30 on the TICS, the Dementia Questionnaire will be administered to the participant's proxy. & At follow-up, the EPrime computerized testing will be administered at the 18 month visit; a small number of participants will complete this at their 30 month visit rather than their 18 month visit. @Includes lipid and metabolic panel, and CBC; @@The 6-month phlebotomy is performed only at the following sites: Northwestern University, Tufts University, University of Pittsburgh, and Wake Forest University. Urine samples are not collected at the 6-month visit. %The proxy ADL questionnaire is administered when a participant is not available to complete a follow-up assessment or is deemed to be cognitively impaired based on the Six-item screener. \$The Assistive Device Questionnaire is administered at any visit at which the 400 m walk test is not attempted. \*\*Measures to be obtained at closeout only if the measures were missed at the scheduled follow-up or if the scheduled follow-up visit occurred more than one year to the closeout visit.

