**(e) Dyspnea.**

Dyspnea will be assessed with a modified version of the ATS-DLD-78-A questionnaire [ATS-DLD-78-A Adult Dyspnea Questionnaire. at <http://www.cdc.gov/niosh/respire.html>] and the Borg index for Dyspnea.

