**Tertiary Aim #5** will be assessed using a logistic regression model with adjustment for Field Center and gender for the outcome of dyspnea. Ventilatory capacity will be examined using two types of mixed model analysis of variance models. First, we will examine for different post-baseline mean levels of FVC and FEV1 using a model adjusting for the baseline level, time (categorical), Field Center, and gender. We will account for within-person correlation using a subject random effect. Second, we will examine for a difference in the rates of decline using a random intercept/random slope mixed model.

**Tertiary Aims #6 and 7** will be assessed using Cox proportional hazards models, stratified by Field Center and gender. Failure time is measured from the time of randomization to the occurrence of a pulmonary disorder (Aim 6) or combined cardiovascular event (Aim 7).

**Tertiary aim #8** will be to explore time by intervention interactions on the SPPB score and 400 m walk speed endpoints. Separate estimates of the intervention effect will be obtained for participants with different planned lengths of intervention. This will be achieved by introducing variables representing periods of randomization (i.e., groupings of consecutive months) into the repeated measures models for SPPB score and 400 m walking speed and exploring the interaction between these variables and the intervention effect. There may be some confounding between other factors and the month of randomization (e.g., staff familiarity with the intervention); however, this analysis could be important in determining how length of intervention may relate to efficacy. We also will use interaction terms like these to estimate intervention effects for 1-year epochs across follow-up to examine their consistency over time.

**Tertiary aim #9** will be to explore whether the relative effect of the PA intervention on measures of cognitive function varies according to baseline level of global cognitive function. Separate estimates of the intervention effect on measures of cognitive function will be obtained for participants grouped by baseline 3MS (<90 versus  $\geq 90$ ). Tests of interaction will be used to compare any differences between these groups.

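### The Tertiary Aim #5 dyspnea model leaves out the baseline symptom answers that the trial already collects; the comparison stays valid but gives up some power

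*Protocol*

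**What the plan says.** Section 3.1.2 of the protocol hypothesizes that the physical activity program "Reduces dyspnea and improves ventilatory capacity". Section 10.3.6(e) names two instruments: "Dyspnea will be assessed with a modified version of the ATS-DLD-78-A questionnaire", together with the Borg index.

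On the questionnaire, section 6.2.17 describes the longer entry form: "A modified version of the ATS-DLD-78-A questionnaire assesses respiratory symptoms, prior cardiopulmonary illnesses, occupational history, and smoking exposure". It then says: "At follow-up, the ATS-DLD-78-A will be further modified to include only respiratory symptoms, and smoking status". The Table 10.1 row "Pulmonary questionnaires, ventilatory capacity" is marked at SV2 and at months 6, 18 and 30. Respiratory symptoms are therefore recorded both before and after randomization.

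On the Borg index, section 6.2.17 says that it "will be administered immediately after the 400 m walk each of the follow-up clinic visits". Table 10.1 has no separate Borg row. A footnote to the table places a baseline walk before randomization: "The 400 m walk test can be administered either at the end of SV1 or at SV2".

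On analysis, section 12.2 says that Tertiary Aim #5 "will be assessed using a logistic regression model with adjustment for Field Center and gender for the outcome of dyspnea". For FVC and FEV1 the same paragraph includes the baseline level, time, field center and gender.

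**The concern.** The hypothesis is about reducing a symptom that some participants will already have. Section 4.2.2 excludes lung disease that needs regular corticosteroid pills or injections or supplemental oxygen, and it excludes severe shortness of breath on the 400 m walk. Milder dyspnea is still eligible. Entry status should then predict follow-up status, and a model that ignores a prognostic covariate already in hand has less power than one that uses it.

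This is a stated covariate set, not a detail left open. Section 12.2 lists the dyspnea covariates and then gives a different list, with baseline, for the other half of the same aim. Baseline covariates also appear in its models for DSST/HVLT, ADL disability, the cognitive composite and MCI/dementia (itself a logistic model). Dyspnea departs from that practice and no reason is given. What is at stake is the sensitivity of one exploratory comparison.

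**Working it through.** **1. Is a usable baseline value available?** Yes. Respiratory symptoms are in both the entry form and the shortened follow-up form (6.2.17), and Table 10.1 marks SV2.

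**2. Benchmark from the protocol's own figures.** No power is stated for dyspnea. The nearest stated figures are in Table 3.3.6 for ventilatory capacity, the other half of Tertiary Aim #5. Inputs from section 3.3: SD 0.57 (FEV1) and 0.66 (FVC), baseline-adjusted ANCOVA, 1,600 participants, hence 800 per arm. I take two-sided alpha 0.05.

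Power = Φ( δ / [SD·√(1−r²)·√(2/n)] − 1.96 )

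FEV1, r = 0.5, δ = 0.05: adjusted SD = 0.57 × 0.866 = 0.494; standard error = 0.494 × √(2/800) = 0.0247; δ/SE = 2.03; power = 52.6%, against 53% stated. With 800 per arm and no loss to follow-up, all 12 cells agree within 2 points. Setting r = 0 removes the baseline term: for FEV1 the standard error is 0.57 × 0.05 = 0.0285, δ/SE = 1.75, power 42%; for FVC it is 0.66 × 0.05 = 0.033, δ/SE = 1.52, power 33%.

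| δ = 0.05 | r = 0.3 | r = 0.5 | r = 0.7 | no baseline |
|---|---|---|---|---|
| FEV1, stated | 45% | 53% | 69% | 42% (computed) |
| FVC, stated | 36% | 42% | 56% | 33% (computed) |

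Dropping baseline from that calculation would cost 3 to 27 points for FEV1 and 3 to 23 for FVC. This shows the direction; it is not an estimate for a binary dyspnea outcome.

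**3. Illustration for dyspnea (assumed inputs).** Retention of 84.6% at 2 years (section 3.3) gives 1,600 × 0.846 = 1,354, or 677 per arm. Prevalence, effect and correlation are assumptions. Each scenario is 1,500 simulated trials with a logistic Wald test at 0.05; Monte Carlo error is about 1 point.

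*Set A:* 30% baseline dyspnea, conditional odds ratio 0.67.

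| Control-arm follow-up dyspnea if baseline yes / no | phi | Without baseline | With baseline | Gain |
|---|---|---|---|---|
| 0.55 / 0.20 | 0.35 | 83.1% | 86.7% | 3.6 |
| 0.60 / 0.17 | 0.43 | 74.8% | 83.4% | 8.6 |
| 0.70 / 0.12 | 0.58 | 59.3% | 76.9% | 17.6 |

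*Set B:* control-arm prevalence 20%, 30% or 50%, with the effect chosen to give the unadjusted model about 80% power.

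| Latent correlation | phi | Without baseline | With baseline | Gain |
|---|---|---|---|---|
| 0.5 | 0.29–0.33 | 80–82% | 83–86% | about 3 |
| 0.7 | 0.46–0.49 | 80% | 86–90% | 6–10 |
| 0.85 | 0.61–0.65 | 80–81% | 94–96% | 13–15 |

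With only 10% baseline prevalence and phi of about 0.33 to 0.39, power rises from 47% to 51% and from 43% to 50%. Over all these scenarios the gain is roughly 3 to 18 points.

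**4. The sample size used.** Month 24 is not a questionnaire visit. At 8% loss per year, month 18 gives 1,600 × 0.92^1.5 = 1,412. Month 30 gives at most 1,600 × 0.92^2.5 = 1,299, since some participants close out before then. Rerunning Set A at these sizes moved the gains by no more than 2 points.

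**5. Validity without the covariate.** With no treatment effect, 4,000 trials per Set A scenario gave rejection rates of 4.4%, 5.1% and 5.3% for the unadjusted model, consistent with the nominal 5%.

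**6. What the covariate does to the estimate.** In the third Set A scenario, control prevalence is 0.3 × 0.70 + 0.7 × 0.12 = 0.294. An odds ratio of 0.67 within each baseline group gives treated risks of 0.610 and 0.084, hence 0.3 × 0.610 + 0.7 × 0.084 = 0.242 overall. The marginal odds ratio is (0.242/0.758)/(0.294/0.706) = 0.77, against 0.67 conditionally. The two models estimate different quantities.

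**The case against.** The strongest reply is that nothing here is wrong. Randomization is stratified by field center and gender, the planned model adjusts for exactly those two factors, and its p-value already allows for chance imbalance in entry dyspnea. That stands. A reader might infer that leaving baseline out biases the result, or that a follow-up difference could not be told apart from one present at entry; the design and step 5 do not support this.

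Second, the size of the loss does not come from the documents. That stands too. The upper end needs the highest assumed correlation. Nor do the inputs say that follow-up dyspnea is mostly carried over from entry: phi of 0.35 to 0.58 means 12% to 34% shared variance (0.35² to 0.58²). The exclusion for severe shortness of breath also narrows entry dyspnea. The simulation uses one follow-up reading, whereas three are scheduled.

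Third, a reader might infer that the Borg rating is definitely absent at baseline. Follow-up only is the more natural reading of 6.2.17, but it rests on one imperfect sentence. The index sits under the pulmonary questionnaires heading, the matching row of Table 10.1 is marked at SV2, and no separate Borg analysis is stated. This supports a request for clarification and no more.

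Fourth, covariates could be left to the SAP. That carries less weight here, because the protocol names the set and names a different one for the companion outcome.

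**Conclusion.** The point holds as one of efficiency. The dyspnea model omits a baseline value that the trial collects, against the protocol's own practice in the same paragraph and in several other models. The planned comparison is valid but less powerful than it could be at no cost. Under assumed prevalence, effect and correlation the loss is roughly 3 to 18 points for phi of about 0.3 to 0.6; no dyspnea-specific figure can be derived from the protocol. Priority is minor: dyspnea is a tertiary outcome that section 12.1 sets out to explore, it carries no power claim, and the primary conclusion is untouched.

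**What to change.** In section 12.2, Tertiary Aim #5, add dyspnea status from the SV2 questionnaire, built from the same symptom items as the follow-up outcome, to field center and gender in the logistic model. State that the reported effect is then an odds ratio conditional on baseline dyspnea. Do this before anyone sees outcome data by arm, so that adjusted and unadjusted results are not chosen between afterwards. The cost is one covariate from data already collected, with no added visit or participant burden.

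Optionally, clarify in section 6.2.17 and Table 10.1 whether the Borg rating is also taken after the baseline 400 m walk. If it is, use it as the covariate in any Borg comparison. If it is not, adding it would mean one rating after a walk already performed; participants enrolled before the change would lack it, and the questionnaire covariate could serve for them.

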### 3. Overview of Trial Design

#### 3.1. Design

The LIFE Study is a **multicenter single-blind RCT** involving physical activity vs. a successful aging program, with an average follow-up of 2.7 years (range 1.9-3.5 years or 23-42 months) in 1600 non-disabled, community-dwelling persons age 70-89 years across 8 Field Centers.

The **inclusion criteria** are (1) age 70 to 89 years; (2) summary score <10 on the EPESE short physical performance battery (SPPB); (3) sedentary lifestyle; (4) ability to complete the 400 m walk test within 15 minutes without sitting or the help of another person, or the use of a walker; and (5) willingness to be randomized to either intervention group. The **exclusion criteria** reflect conditions that may interfere with the conduct of the physical activity program. LIFE plans to recruit 65% women and 22.5% minorities.

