Of primary interest is a comparison of the probability of being classified as having major mobility disability at two consecutive assessments. This outcome will be analyzed using transitional models for categorical endpoints. A first-order Markov model will be used to compare between intervention groups the probability of being classified in the major mobility disability category at a subsequent visit, given a participant's previous classification state. Validity of the first-order versus higher-order Markov assumptions will be explored within these models.

**Secondary aim #4** will be to assess the relative effect of randomization to the intervention on the combined outcome of major mobility disability or death.

The main comparisons of intervention groups with respect to the distribution of time until the first post-randomization occurrence of the combined outcome of major mobility disability or death will be based on survival analyses. To compare intervention arms, we will use a likelihood ratio test from a Cox regression model, stratified by field center and gender. Failure time is measured from the time of randomization.

**Secondary aim #5** will be to assess the relative effect of randomization to the intervention on the proportion of 400 m walk failures over time.

This analysis will use the repeated 6-month indicators of 400 m walk status (rather than the time until the initial failure) and compare the average proportion of participants in each intervention group that fail the 400 m walk across all time points using generalized estimating equations (GEEs) that account for the dependency between repeated measures. Odds ratios for the association between 400 m walk status and intervention will be estimated after adjusting for field center, gender, a follow-up time effect, and an intervention effect. This approach is most consistent with 400 m walk serving as a marker of functional status and the trial examining whether lifestyle interventions may alter the distribution of this construct.

**Secondary aim #6** will be to assess the relative effect of randomization to the

intervention on the disability in activities of daily living.

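### Tertiary Aim #5 names a logistic model for dyspnea without visit, baseline or within-person term, although the questionnaire is repeated at 6, 18 and 30 months; logistic GEE would be the better choice

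*Protocol*

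**What the plan says.** In Protocol section 12.2, Tertiary Aim #5 "will be assessed using a logistic regression model with adjustment for Field Center and gender for the outcome of dyspnea". Nothing else is said about the dyspnea analysis: no visit, baseline or subject term, no robust variance, and no choice of a single visit or per-person summary.

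Two instruments feed this outcome. Section 10.3.6(e) states "Dyspnea will be assessed with a modified version of the ATS-DLD-78-A questionnaire" and adds the Borg index. In Table 10.1 the row "Pulmonary questionnaires, ventilatory capacity" is marked at SV2 and at months 6, 18 and 30. The Borg index, according to section 6.2.17, "will be administered immediately after the 400 m walk each of the follow-up clinic visits".

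The rest of Tertiary Aim #5 covers FVC and FEV1, collected at the same visits as the questionnaire. The first of its two models adjusts for baseline level, categorical time, Field Center and gender, and the protocol adds: "We will account for within-person correlation using a subject random effect". For the repeated pass/fail status on the 400 m walk, Secondary aim #5 compares the groups "using generalized estimating equations (GEEs) that account for the dependency between repeated measures".

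**The concern.** Participants are randomized individually, and each can contribute up to three follow-up questionnaires plus a baseline one. The named model does not reflect this, although section 12.2 handles repeated data explicitly in several other places. An analyst who follows the text must choose between pooling the visits, picking one visit, or collapsing each person to ever/never dyspnea.

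These choices are not equivalent. Pooling counts one person's answers as those of different people, so the standard error is too small and a chance difference could be read as support for the hypothesis that the program reduces dyspnea. The other two give a valid test but use the collected data less well. None of them uses the baseline questionnaire.

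**Working it through.** **Inputs from the protocol.** Sample size 1,600 (section 3.3). Loss to follow-up 8% per year (section 3.3). Follow-up "range 1.9-3.5 years or 23-42 months" (section 3.1). Questionnaire visits at months 6, 18 and 30 (Table 10.1).

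**Inputs that are assumed.** The protocol gives no dyspnea prevalence, within-person correlation, effect size, power or significance level, so there is no stated figure to reproduce. Assumed: prevalence 30%, correlation 0.3 to 0.7, odds ratio 0.75 at every visit, two-sided 5% (the level stated for other tertiary outcomes).

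**Visits per person.** With follow-up uniform over 23-42 months, the share that can reach month 30 is (42 - 30)/(42 - 23) = 12/19 = 63%. Everyone can reach months 6 and 18. Without loss this gives 1 + 1 + 0.63 = 2.63 visits per person. With 8% annual loss it gives 0.92^0.5 + 0.92^1.5 + 0.63 × 0.92^2.5 = 0.96 + 0.88 + 0.51 = 2.35.

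**Type I error if visits are pooled as independent rows.** With m visits and correlation ρ, the variance is understated by the factor 1 + (m - 1)ρ, so the actual error is 2[1 - Φ(1.96/√(1 + (m - 1)ρ))].

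| ρ | m = 3 (complete data) | m = 2.63 (staggered follow-up) |
|---|---|---|
| 0.3 | factor 1.60, error 12.1% | factor 1.49, error 10.8% |
| 0.5 | factor 2.00, error 16.6% | factor 1.81, error 14.6% |
| 0.7 | factor 2.40, error 20.6% | factor 2.14, error 18.0% |

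Simulation with the trial's follow-up and loss, at 30% prevalence, gives about 10-17% over the same correlations. A separate simulation at 25% prevalence, which included site and gender terms, gave 11.4%, 12.4% and 14.0% at correlations of 0.22, 0.40 and 0.57. Adjusting for Field Center and gender therefore does not remove the problem. In that simulation (1,000 runs per setting, simulation error about 1.4 points), three alternatives stayed close to 5% on the questionnaire schedule: participant-clustered variance 4.2-6.4%, ever/never 4.6-5.8%, single visit 4.6-5.8%.

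**Power of the valid options** (simulation; prevalence 30%, odds ratio 0.75):

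| Analysis | Correlation about 0.5 | Range over 0.3-0.7 |
|---|---|---|
| Month 18 only | about 65% | 65-68% |
| Ever/never over all visits | about 78% | 75-84% |
| Logistic GEE over months 6, 18, 30 | about 83% | 78-91% |

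At correlation 0.5 the gain from GEE is 83 - 65 = 18 points over the single visit and 83 - 78 = 5 points over ever/never. These runs had no baseline dyspnea term, so they do not measure what baseline adjustment would add.

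**The case against.** The strongest reply is that the protocol never says that visits are pooled, and that its own pattern points the other way. Where repeated rows are meant, it names GEE, a mixed model or a subject random effect. Plain logistic regression appears for conversion to MCI or dementia, which is one outcome per participant. Sleep-wake disturbance, also measured at 6, 18 and 30 months, is reduced to one event per person. Logistic regression for a binary outcome is not wrong in itself, and it can be fitted by GEE. The binary definition and the visit to be analysed are details that a statistical analysis plan commonly supplies.

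Much of this stands. A reader might infer that the plan itself inflates the false-positive rate two- to six-fold or else discards most of its visits. The documents do not support that. Pooling is not stated, and ever/never is a third route that uses every visit and keeps about 5% error. The upper end of the range would also require the Borg rating to be dichotomised and pooled over six visits at a correlation of about 0.7 (31% simulated, and 31/5 = 6.2). Nothing in the protocol says that the Borg rating enters the logistic model at all.

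What the reply does not remove is that the protocol fixes a model and its covariates, and that each way of applying it to these data is inferior to GEE. Ever/never has a further weakness: with 23 to 42 months of follow-up, people have unequal numbers of chances to report dyspnea, and someone who improves after one early report still counts as a case.

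**Conclusion.** The point holds in a limited form. The dyspnea model in Tertiary Aim #5 does not match the repeated collection of the questionnaire, and a better method already stands in the same section. Pooling, if it were done, would give about 10-17% type I error. The valid readings cost power: about 18 points for a single visit and 5 points for ever/never at correlation 0.5, with the loss against ever/never narrowing to about 3 points (78% against 75%) at correlation 0.7. All of these figures rest on assumed prevalence, correlation and a constant odds ratio, and on dropout unrelated to dyspnea. The direction is secure, the exact size is not.

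Severity is minor. Section 12.1 frames the tertiary aims as exploratory, no power is claimed for dyspnea, and the primary and secondary conclusions are untouched.

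**What to change.** In section 12.2, Tertiary Aim #5, replace the dyspnea model with a logistic GEE with robust variance clustered on participant, over the questionnaire visits at months 6, 18 and 30, with terms for intervention, visit, Field Center, gender and baseline (SV2) dyspnea.

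Keep the Borg ratings as a separate supportive analysis with the same participant-level clustering. They exist only when the 400 m walk is attempted, so missing ratings may depend on dyspnea itself, and GEE does not correct for that.

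The cost is one or two sentences of analysis text. No data, visits or participants are added, and the method is already used in Secondary aim #5. The downside is the usual GEE assumption about missing visits.
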